## Abstract

**Background:**

Patients with dementia and their caregivers could benefit from advance care planning though may not be having these discussions in a timely manner or at all. A prognostic tool could serve as a prompt to healthcare providers to initiate advance care planning among patients and their caregivers, which could increase the receipt of care that is concordant with their goals. Existing prognostic tools have limitations. We seek to develop and validate a clinical prediction tool to estimate the risk of 1-year mortality among hospitalized patients with dementia.

**Methods:**

The derivation cohort will include approximately 235,000 patients with dementia, who were admitted to hospital in Ontario from April 1st, 2009, to December 31st, 2017. Predictor variables will be fully prespecified based on a literature review of etiological studies and existing prognostic tools, and on subject-matter expertise; they will be categorized as follows: sociodemographic factors, comorbidities, previous interventions, functional status, nutritional status, admission information, previous health care utilization. Data-driven selection of predictors will be avoided. Continuous predictors will be modelled as restricted cubic splines. The outcome variable will be mortality within 1 year of admission, which will be modelled as a binary variable, such that a logistic regression model will be estimated. Predictor and outcome variables will be derived from linked population-level healthcare administrative databases. The validation cohort will comprise about 63,000 dementia patients, who were admitted to hospital in Ontario from January 1st, 2018, to March 31st, 2019. Model performance, measured by predictive accuracy, discrimination, and calibration, will be assessed using internal (temporal) validation. Calibration will be evaluated in the total validation cohort and in subgroups of importance to clinicians and policymakers. The final model will be based on the full cohort.

**Discussion:**

We seek to develop and validate a clinical prediction tool to estimate the risk of 1-year mortality among hospitalized patients with dementia. The model would be integrated into the electronic medical records of hospitals to automatically output 1-year mortality risk upon hospitalization. The tool could serve as a trigger for advance care planning and inform access to specialist palliative care services with prognosis-based eligibility criteria. Before implementation, the tool will require external validation and study of its potential impact on clinical decision-making and patient outcomes.

**Trial registration:**

NCT05371782.

## Background

### Advance care planning in dementia

Patients with dementia and their caregivers are faced with difficult healthcare decisions, especially at advanced stages of disease. These decisions are made more difficult by the inevitability that patients with dementia will lose capacity to make them [1]. Early engagement in advance care planning facilitates timely shared decision-making between a patient, their substitute decision maker, and their healthcare provider. There is evidence for the benefit of advance care planning among dementia patients. A systematic review of advance care planning in this patient population demonstrated an association with an increase in documentation of advance directives, the number of discussions about goals of care, and the receipt of goal-concordant care [2]. Despite these benefits, there is a deficiency of advance care planning in this patient population [3, 4]. This may be caused by a variety of barriers, including uncertainty about the optimal timing of advance care planning, difficulty in planning for an uncertain future, patients’ and caregivers’ lack of knowledge about dementia, difficulty in the assessment of decisional capacity among dementia patients, and the possibility that preferences may change over time [5]. A lack of advance care planning may enable decisions that result in frequent acute care utilization [6–12], the pursuit of life-prolonging interventions [13–15], and absent or delayed access to specialist palliative care [11, 16–19] in the advanced stages of disease. By identifying individuals with dementia who have a high risk of mortality, a prognostic tool could serve as a prompt to healthcare providers to initiate advance care planning among patients and their caregivers. It could also trigger a referral to specialist palliative care services if needs are complex. This could result in the receipt of care that is concordant with a patient’s goals.

### Prognostic tools among hospitalized patients with dementia

The hospital is a pragmatic setting in which a prognostic tool among patients with dementia could be implemented. Patients with dementia are frequently hospitalized, especially as they approach the end of life [6–12], such that a hospital-based prognostic tool could be applied to a high proportion of this patient population. In addition, hospitalization may represent a significant point of inflection among patients with dementia. Specifically, hospitalized patients with dementia have a higher risk of mortality and readmission than patients without dementia [20]. In addition, hospitalizations among patients with dementia who were living at home may result in a discharge to a long-term care facility [21, 22]. Therefore, hospitalization could serve as a touchpoint to have a discussion about the expected disease trajectory, informed by the output of a prognostic tool.

There have been 3 attempts to develop a prognostic tool among hospitalized patients with dementia [23–25]. They have limitations that decrease their clinical utility. First, the studies have methodological weaknesses regarding variable selection [24], specification of continuous variables [24, 25], and handling of missing values [25]. Second, the tools had a limited number of predictor variables, and none of them included non-linear or interaction terms. Therefore, they may not be sufficiently complex to capture the nuances of mortality risk prediction in this patient population. Third, their performance was assessed in terms of discrimination, which ranged from poor to acceptable. However, it was not or inadequately assessed and/or reported in terms of calibration, which provides an indication of a prognostic tool’s ability to make accurate predictions for new patients. All of the models were judged to be at high risk of bias based on the Prediction model Risk Of Bias ASsessment Tool (PROBAST) [26]. Otherwise, one study included clinically meaningful variables, but ones that were collected through a comprehensive geriatrics assessment, which limits its utility [23]. Another study sought to predict mortality among only patients with dementia who underwent surgery for a hip fracture, which limits its generalizability [25]. None of these models have been externally validated or are used in practice to our knowledge.

### Objectives

This study seeks to develop and validate a clinical prediction tool to estimate the risk of 1-year mortality among a cohort of patients with dementia hospitalized in Ontario from April 1st, 2009, to March 31st, 2019. The model will include a comprehensive list of clinically meaningful variables that are routinely collected in population-level healthcare administrative databases, and non-linear and interaction terms. In addition, it will comprise an inclusive cohort of hospitalized patients with dementia, not limiting it to those with specific complications. Model performance will not only be assessed in terms of predictive accuracy and discrimination*,* but also in terms of calibration in the validation cohort and in predefined subgroups of importance to clinicians and policymakers. Finally, the protocol will adhere to recommendations for the development [27] and reporting [28, 29] of prognostic studies.

## Methods/design

### Study design

The model will be derived and validated using population-level data in the healthcare administrative databases at ICES in Ontario, Canada. Ontario is Canada’s most populous province, comprising 14.8 million residents [30]. This model, which seeks to predict mortality among hospitalized patients with dementia, would be well served by population-based data in Ontario, since the high rates of both acute care utilization [31] and mortality [32] among patients with dementia have been established therein. Patients or the public were not involved in the design and will not be involved in the conduct, reporting, or dissemination of this study. However, they will be involved in the implementation of the clinical prediction tool.

In Ontario, healthcare is administered through a primarily public system, which is accessible to all individuals by means of a universal health insurance program. ICES houses multiple databases that include data on all individuals in Ontario who are eligible for the program. Of most interest to this study is the Discharge Abstract Database (DAD), which is maintained by the Canadian Institute for Health Information [33], and from which predictor variables will be identified. This database includes information on individuals who have been admitted to any acute care facility in Ontario, which has been collected from discharge summaries by trained abstractors. The presence of the DAD in all other provinces and territories of Canada lends itself to the application of this tool beyond Ontario.

### Eligibility criteria

Individuals with dementia will be identified using a validated algorithm to identify cases based on a combination of hospital codes, physician claims, and prescribed medications that are specific to dementia [34]. This algorithm was validated and found to be sufficiently sensitive (79.3%) and highly specific (99.1%) [34]. Individuals will be included if they were hospitalized at least once from April 1st, 2009, to March 31st, 2019. Exclusion criteria will be age < 65 years at the time of admission to exclude phenotypes of early-onset dementia, which may be informed by a different profile of predictor variables; no age or sex at the time of admission; ineligibility for universal health insurance at the time of admission or for ≥ 3 months before admission; and death recorded as having happened before or at the time of admission. If a patient was admitted more than once during the 10-year accrual window, then only the first admission will be included to avoid survival bias.

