Second, we identified variables in existing prognostic indices [23–25] or that have an established association with mortality based on etiological studies [45–57] among hospitalized patients with dementia. The existing prognostic indices were identified through a systematic review using a single electronic database (PubMed), in addition to hand-searching of each of their reference lists. The etiological studies were identified in a recent scoping review of prognostic factors in dementia [58]. We then identified, where possible, correlates of these variables in the DAD. Finally, we reviewed all variables in the DAD to identify those that, based on subject-matter expertise, could inform mortality risk prediction in this patient population but are not present in either the mHOMR or the literature. Specifically, our research team includes clinical expertise in internal medicine, family medicine, public health, and palliative medicine. Since the ultimate objective is to have the clinical tool generate a risk of 1-year mortality at the time of admission, predictor variables that would not be known at the time of admission (e.g., admitting diagnosis, length of stay) were not considered. Variables with narrow distributions or insufficient variation will be excluded (e.g., binary variables for which one level has few or no observations). Variables with a high proportion of missing values (> 50%) will be excluded. While multiple imputation (see Missing data) may perform well if a variable has > 90% missingness [59], a variable with > 50% missing may be of poor quality and result in bias. A total of 87 predictor variables were identified and categorized as follows: sociodemographic factors (3), comorbidities (51), previous interventions (8), functional status (11), nutritional status (7), admission information (4), previous health care utilization (3) (Table 1). For comorbidities and previous interventions, a 3-year lookback window will be used, which is in keeping with the most recent iteration of the mHOMR [60].

**Table 1 Tab1:** Prespecification of predictor variables for a mortality risk prediction tool among hospitalized patients with dementia with initial degrees of freedom allocation

Variable	Scale	Initial variable specification	Degrees of freedom
Sociodemographic factors			
Age	Continuous	5-knot spline: valid range: 65 to 105 years	4
Sex	Categorical	Male; female	1

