Radiotherapy	Categorical	Yes; no	1
Tracheostomy	Categorical	Yes; no	1
Functional status			
Hospital Frailty Risk Score	Continuous	5-knot spline: valid range 0 to 99	4
Dysphasia and aphasia	Categorical	Yes; no	1
Dysarthria and anarthria	Categorical	Yes; no	1
Dysphagia	Categorical	Yes; no	1
Dependence on wheelchair	Categorical	Yes; no	1
Blindness	Categorical	Yes; no	1
Hearing loss	Categorical	Yes; no	1
Hospital-based occupational therapy consultation in past 3 years	Categorical	Yes; no	1
Hospital-based physiotherapy consultation in past 3 years	Categorical	Yes; no	1
Hospital-based social worker consultation in past 3 years	Categorical	Yes; no	1
Hospital-based speech language pathology consultation in past 3 years	Categorical	Yes; no	1
Nutritional status			
Weight	Continuous	5-knot spline	4
Height	Continuous	5-knot spline	4
Parenteral nutrition	Categorical	Yes; no	1
Feeding tube	Categorical	Yes; no	1
Anorexia	Categorical	Yes; no	1
Abnormal weight loss	Categorical	Yes; no	1
Volume depletion	Categorical	Yes; no	1
Admission information			
Admitting service	Categorical	15 categories: General internal medicine; Cardiology; Gastroenterology; Palliative care; Medical oncology; General surgery; Cardiovascular surgery; Neurosurgery; Orthopedic surgery; Plastic surgery; Thoracic surgery; Trauma; Urology; Gynecology; Psychiatry	14
Admission urgency	Categorical	3 categories: elective; urgent, without ambulance; urgent, with ambulance	2
Admission directly to ICU	Categorical	Yes; no	1
Urgent 30-day readmission	Categorical	Yes; no	1
Previous healthcare utilization			
ED visits in past 12 months	Ordinal	7 categories: 0, 1, 2, 3, 4, 5, 6 +	6
Admissions by ambulance in past 12 months	Ordinal	4 categories: 0, 1, 2, 3 +	3
Hospital-based palliative care in past 3 years	Categorical	Yes; no	1

Age will be interacted with all variables except those listed under sociodemographic factors, admission information, and previous health care utilization; renal failure will be interacted with dialysis; each site of malignancy will be interacted with chemotherapy

*ICU* Intensive care unit, *ED* Emergency department

The model will include age interactions with variables that represent comorbidities and previous interventions, since the association of these variables with mortality may vary with age. It will also include interactions of diseases with corresponding treatments, including kidney dysfunction with dialysis, and malignancy with chemotherapy.

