**Fig. 1 Fig1:**
[figure not shown]
**A** A patient with dementia is hospitalized, at which point a risk of 1-year mortality is automatically calculated by the computer. **B** If the risk of mortality is below a user-defined threshold, then the admitting team is not alerted. The threshold is based on the capacity of medical and specialist palliative care teams to act on the alert. **C** If the risk of mortality is above the threshold, then the admitting team is alerted. **D** The alert could prompt the admitting team to initiate advance care planning (primary palliative care). **E** The alert could prompt the admitting team to refer to specialist palliative care if needs are complex

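### Keeping only each patient's first admission conflicts with predictors that need an earlier stay and leaves performance at repeat admissions, where the tool would also run, unestimated

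*Protocol article*

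**What the plan says.** The Eligibility criteria section accrues patients over ten years: "Individuals will be included if they were hospitalized at least once from April 1st, 2009, to March 31st, 2019". It then keeps one admission each. If a patient was "admitted more than once during the 10-year accrual window, then only the first admission will be included"; the reason given is survival bias. Dementia is identified by an algorithm using a "combination of hospital codes, physician claims, and prescribed medications that are specific to dementia", but the text does not say whether the retained admission is the first of any kind or the first after dementia has been ascertained. It also does not say whether the rule is applied once to the whole window or separately in the derivation and validation cohorts.

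The Study design section names the DAD, a record of acute-care admissions, as the database "from which predictor variables will be identified". The Identification of predictors section adds: "For comorbidities and previous interventions, a 3-year lookback window will be used". Table 1 includes "Urgent 30-day readmission", ambulance admissions over 12 months, and four kinds of hospital-based consultation and hospital-based palliative care over 3 years.

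On use, the Fig. 1 legend says: "A patient with dementia is hospitalized, at which point a risk of 1-year mortality is automatically calculated by the computer". The Model presentation and Conclusion sections describe the same trigger. None of them restricts it to a first admission.

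**The concern.** Several predictors describe what happened at earlier hospital stays, while the index rule selects the admission that has no earlier stay in the window. Early index dates can still look back before April 2009; later ones, on the literal reading, cannot find an admission at all. The same predictor would then carry different information in early derivation years than in later derivation years and in validation.

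The second conflict is with use. The Background calls patients with dementia frequently hospitalized, particularly near the end of life, so repeat admissions will be a regular occasion for the alert. If they are in neither cohort, the reported c-statistic and calibration say nothing direct about them, although the Assessment of performance section presents the temporal validation as evidence of transportability.

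**Working it through.** **Inputs.** The window is 1 April 2009 to 31 March 2019 (3652 days). Derivation runs to 31 December 2017 (3197 days) with about 235,000 patients. Validation is 1 January 2018 to 31 March 2019 (455 days) with about 63,000. Dates are from the Abstract and Eligibility criteria, counts from Sample size.

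**1. The plan's own split.** 235,000 + 63,000 = 298,000, and the shares are 235/298 = 78.9% and 63/298 = 21.1%. This agrees with the stated total and the stated split of about 80% and 20%.

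**2. Literal reading: no earlier admission since 1 April 2009.** An earlier admission can fall inside a look-back of length L only if the index date lies within L of the window's start.

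| Look-back | Days | Share of window | Share of derivation period | Share of validation period |
|---|---|---|---|---|
| 30 days (urgent readmission) | 30 | 30/3652 = 0.8% | 30/3197 = 0.9% | 0% |
| 12 months (ambulance admissions) | 365 | 365/3652 = 10.0% | 365/3197 = 11.4% | 0% |
| 3 years (DAD history) | 1096 | 1096/3652 = 30.0% | 1096/3197 = 34.3% | 0% |

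For the remaining 100 − 34.3 = 65.7% of the derivation period, DAD history over 3 years is structurally absent. In validation it is absent throughout, because every patient must have been free of admission since April 2009, at least 8.75 years. These are shares of calendar time, not of patients; the document gives no counts by year.

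**3. Alternative reading: first admission after dementia ascertainment.** Stays before ascertainment can fill the look-back, and a 30-day readmission is possible when such a stay came just before. The history is then restricted, not empty. Later admissions of the same patient with dementia remain excluded from both cohorts.

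**4. Do the counts fit?** Accrual per year = patients / days × 365.25.

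- Derivation: 235,000 / 3197 × 365.25 ≈ 26,800.
- Validation: 63,000 / 455 × 365.25 ≈ 50,600.
- Ratio: (63,000/455) / (235,000/3197) = 1.88. Validation covers 455/3652 = 12.5% of the window but holds 21.1% of patients.

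A rule that takes each patient once, at the first admission in the window, should collect existing cases early and slow down afterwards. That expectation applies to the readings in steps 2 and 3 alike, and the counts run the other way. Growth in the dementia population could push late accrual up, but the document gives no figure for it.

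**5. Could the index have been chosen within each cohort?** That would fit the counts better. Validation patients could then have stays before 2018 in their look-back, some validation admissions would in fact be repeat admissions, and patients could appear in both cohorts. The Eligibility criteria, however, state the rule for the ten-year window as a whole.

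**The case against.** The best defence is that the literal reading may not be what was done. The section defines people with dementia before it picks an admission, so first admission with dementia is a natural reading, and the counts count against the literal one. This stands: an empty look-back is a consequence of one reading, not an established fact.

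A reader might go further and infer that 51 + 8 + 4 + 1 + 1 + 1 = 66 of the 87 predictors are constant in validation (comorbidities, interventions, consultations, readmission, ambulance admissions, palliative care). The document does not support that. It needs the literal reading and also history taken only from the DAD, whereas the Abstract speaks of linked databases and the Limitations section says predictors come primarily, not solely, from the DAD. Emergency department visits need no admission in any case.

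The plan also drops predictors with too little variation, which would probably remove the readmission variable. That is a partial answer. A comorbidity visible in the early derivation years could pass the screen and still be empty later, and no screen on predictors brings the repeat admissions back.

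One row per patient is a defensible choice for derivation. It keeps observations independent and does not over-weight people who survive to be admitted often. Finally, external validation and impact studies are required before implementation. That limits the harm, but nothing in the plan directs those studies to repeat admissions.

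**Conclusion.** The point holds as an unreconciled conflict within the protocol. As written, the index rule does not fit the readmission and look-back predictors, and it leaves repeat admissions out of derivation and validation while the intended use includes them. The exclusion of repeat dementia admissions follows from both first-in-window readings. The near-total loss of look-back history (0.8% of the window for 30-day readmission, nothing after March 2012 for 3-year DAD history) rests on the literal reading alone. The 1.88-fold difference in accrual means the rule as described needs explaining whichever reading is meant.

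Two further inferences should be resisted. A reader might conclude that the model is neither built nor validated on the admissions where it will run. The tool will also run at first admissions, and those are in both cohorts; the gap is repeat admissions. A reader might also try to size the miscalibration. If 1-year mortality at repeat admissions were 5 to 10 points above the cohort's 103,000/298,000 = 34.6%, dividing the rates gives 0.346/0.396 − 1 = −13% and 0.346/0.446 − 1 = −22%. The 5 to 10 points are assumed, and the division treats the model as predicting the cohort mean for everyone, ignoring age, frailty, emergency visits, living status and the other covariates. The document gives no repeat-admission counts or death rates, so the size of any miscalibration there cannot be computed.

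**What to change.** Keep the first-admission derivation if wanted, and make three changes.

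1. Define the index admission relative to dementia ascertainment and to each cohort, and reconcile it with the 235,000 and 63,000 counts. A table of look-back predictor frequencies by cohort would show at once what the rule does.
2. Add a validation on all qualifying admissions from January 2018 to March 2019, reporting the c-statistic and calibration separately for first and repeat admissions with patient-clustered intervals. Otherwise, limit the stated intended use to first admissions.
3. Remove urgent 30-day readmission and any other look-back predictor that cannot vary under the final index rule.

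The cost is a re-cut of data already held and clustered intervals. There are real downsides to the all-admissions validation: some of its patients would also be in derivation, and one death can count at several admissions within a year. Clustered intervals cure neither. The all-admissions result should therefore stand alongside the first-admission result, with a check that excludes patients who were in derivation. Making every admission the unit in both periods is a larger and more debatable change, and this point does not require it.
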